#### Analyses for aim three

To study the association between quality of implementation and teacher practices, we will examine whether four domains of fidelity predict change in teacher practices from time one to two. We will use the analytical model similar to the one described above, and model teacher practices at time two as a function of four fidelity measures, controlling for time one teacher practices. To understand how school (inner setting) and teacher (individual characteristics) contextual factors influence teachers’ engagement, exposure and practice, two sets of analyses will be conducted (one for school setting and one for teacher characteristics). Three outcomes (engagement, exposure and change in score on practices) will be analyzed separately. We will model outcomes as a function of school characteristics (such as, leadership, climate and communication) or teacher characteristics (such as self-efficacy).

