### Conceptual framework for implementation

Figure 1 shows the theory of change model for ParentCorps implementation. Our implementation framework is adapted from Reinke *et al*.’s Teacher Training Implementation Model (TTIM) [56] and Damschroder and Lowery’s Consolidated Framework for Implementation Research (CFIR) [36]. While TTIM focuses on multidimensional aspects of intervention fidelity as related to implementation outcomes, CFIR focuses on five domains of contextual factors that may impact implementation outcomes. As per the model, fidelity (including adherence and quality of program implementation, and trainees’ engagement and exposure to the program as defined in the TTIM [56]) may impact teacher implementation of evidence-based practices in the classroom, which in turn will impact student and school outcomes. In addition, five domains of contextual predictors, derived from the CFIR [36] (including intervention characteristics, outer setting, inner setting, individual characteristics and organization process), may impact program implementation (both on fidelity and implementation outcomes) and sustainability. This study focuses on implementation processes and outcomes in the gray shaded boxes in Figure 1. Among the contextual predictors, only the school/inner characteristics (such as school leadership and climate) and individual characteristics (such as teacher factors) will be considered because of the relevance to the school contexts. This study will not focus on contextual predictors related to intervention (ParentCorps) characteristics’ because previous work shows that ParentCorps fits well within Ugandan contexts (see above).

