### Implementation aims and hypotheses

***Firstly, we aim to evaluate the implementation fidelity of Professional Development*****(*****ParentCorps FUNdamentals and Coaching*****) for Ugandan teachers when implemented by Ugandan mental health professionals.** We hypothesize that Ugandan mental health professionals will implement Professional Development with high levels of fidelity.

**Secondly, within the context of an RCT, we aim to evaluate the impact of Professional Development on teacher practices in the classroom during the training school year, and during the following school year with different students.** We hypothesize that, relative to teachers in schools randomized to the waitlist control condition, teachers in intervention schools will use more effective practices in the classroom and these practices will be maintained over time and with a different student population.

**Thirdly, within intervention schools only, we aim to examine the relation between implementation fidelity, context (individual and system factors) and teacher practices.** We hypothesize that higher levels of implementation fidelity will be associated with greater use of effective practices in the classroom, and that positive school and teacher characteristics (such as better school leadership, and higher teacher self-efficacy) will predict higher teacher engagement in Professional Development and greater use of effective practices in the classroom overtime.

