#### Reach

Early childhood teachers will be characterized in terms of demographics, attitudes about use of evidence-based practices and students, parents and school leadership [60, 61], self-efficacy [62] and motivation for change [63].

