#### Implementation

Four domains of implementation fidelity will be assessed. Adherence, the extent to which the mental health professionals deliver the core intervention content and as per program guidelines, will be evaluated based on ParentCorps’ integrity checklists completed by the implementer and videotapes and/or audiotapes of FUNdamentals (all five days) and coaching sessions (five of 14) coded by ParentCorps Academy faculty. Quality of program implementation will be assessed based on teacher satisfaction with the Professional Development and ratings of coaches’ competence. Engagement will be evaluated with two ParentCorps measures of knowledge and practice [40]. Level of knowledge improvement from pre- to post-training will be used as indicators for level of engagement. Exposure will be measured by attendance at ParentCorps FUNdamentals (five days) and coaching sessions (14 sessions).

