#### Analyses for aim two

To evaluate impact on teacher practices, we will apply linear mixed-effect models (apply SAS PROC MIXED procedure [68]) that will adjust for school nesting [69]. We will model post-intervention teacher practices (time two (immediate post intervention or six months after baseline) as a function of intervention, adjusting for time one teacher practices. To evaluate whether teacher practices are maintained over time (time three, seven months after post intervention or the first term of new school year), similar mixed-effect models will be applied. However, only the intervention sample will be analyzed (given that the waitlist control teachers will have received the intervention by time three). We will use repeated data over time (times two and three). We will model teacher practices post-intervention as a linear function of time, adjusting for baseline practices. In addition to random intercepts and slopes for individual teachers, the model will include random effects for schools. If the time effect is not significant, this will indicate maintenance of impact.

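### The aim-three fidelity model names time-one practice as its only control, so context that also affects practice directly would be partly credited to fidelity

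*Protocol article*

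**What the plan says.** **The model.** Under Analyses for aim three, the protocol article will "model teacher practices at time two as a function of four fidelity measures, controlling for time one teacher practices". It adds: "We will use the analytical model similar to the one described above". That points back to the aim-two mixed model, described as one "that will adjust for school nesting", so a school effect is presumably included. Time-one practice is the only covariate named.

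**The hypotheses.** Under Implementation aims and hypotheses, aim three is confined to intervention schools and has two parts:
- "higher levels of implementation fidelity will be associated with greater use of effective practices in the classroom";
- favourable school and teacher characteristics, with leadership and self-efficacy as examples, "will predict higher teacher engagement in Professional Development and greater use of effective practices in the classroom overtime".

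The Conceptual framework section says of contextual predictors that they "may impact program implementation (both on fidelity and implementation outcomes) and sustainability".

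**The measures.** Engagement is one of the four fidelity domains. The Implementation subsection of Study measures defines it thus: "Level of knowledge improvement from pre- to post-training will be used as indicators for level of engagement". Teacher self-efficacy and motivation for change are listed under Reach, and the abstract places individual and contextual factors at baseline.

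**Where context is used.** In aim three these factors enter only two further sets of analyses, with engagement, exposure and change in practice as outcomes. They are not mentioned as covariates when fidelity is the predictor.

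**The concern.** Within the intervention schools nobody is randomised to high or low fidelity. The comparison is between teachers who attended or learned more and those who attended or learned less, and the article itself expects those teachers to differ in self-efficacy and school context. If such a characteristic raises engagement and also raises time-two practice by a route other than engagement, a model without it gives fidelity part of the credit.

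Adjusting for time-one practice does not settle this, because the article expects context to matter for practice over time and plans to analyse its relation to change in practice. Nor does a school random intercept remove differences between teachers in the same school.

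What is at stake is how aim three is read. The conceptual framework presents fidelity as something that may affect classroom practice. A link produced by context could be taken as a reason to invest in attendance and engagement when the driver is teacher confidence or school setting.

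**Working it through.** The article gives no figure for this model, so there is nothing to reproduce. The check asks how often the stated model would find an association when fidelity has no effect.

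**Inputs from the article**
- 40 to 50 teachers per condition (Participants) and five intervention schools (abstract).
- Two-sided test at 0.05, stated for the power analysis and assumed here.
- Baseline outcome plus other covariates explain 20 to 50% of post-intervention variance (Sample size and power). A time-one coefficient of 0.5 gives 0.5² = 25%.

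**Assumptions not in the article**
- One baseline characteristic *u* with standardised path *a* to engagement and direct path *b* to time-two practice.
- *u* independent of time-one practice in the simplest case, and measured without error.

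**Size of the spurious slope**
- Engagement = *a·u* + error, with variance 1. Practice = 0.5 × time one + *b·u* + error, with variance 1. Engagement does not appear in the second equation.
- Given time one, the covariance of engagement and practice is *ab*, so the slope estimated without *u* is *ab*.
- *a* = *b* = 0.3: 0.09. *a* = *b* = 0.4: 0.16. *a* = *b* = 0.5: 0.25.
- The standard error is about √[(0.75 − (*ab*)²)/(n − 3)], where 0.75 = 1 − 0.25. For n = 40 and paths of 0.3 it is √(0.7419/37) = 0.142, so the slope lies 0.09/0.142 = 0.64 standard errors from zero. For paths of 0.4 it is √(0.7244/37) = 0.140, and 0.16/0.140 = 1.14.

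**Rate of significant results with no fidelity effect** (simulation, 6,000 runs, one fidelity measure)

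| *a* = *b* | n = 40, without *u* | n = 40, with *u* | n = 50, without *u* | n = 50, with *u* |
|---|---|---|---|---|
| 0.3 | 9.4% | 4.8% | 11.3% | 5.4% |
| 0.4 | 20.7% | 5.1% | 25.4% | 5.2% |
| 0.5 | 44.3% | 5.2% | 52.4% | 4.6% |

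**All four fidelity measures in the model** (2,000 runs per setting, n = 40 and 50, correlation of *u* with time-one practice 0 or 0.3)
- Both paths 0.3: 8-11%.
- One path 0.3, the other 0.5: 17-23%.
- Both paths 0.5: 39-54%.
- No path to engagement: about 5%. With *u* added: 4.6-5.6%.

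**Weak or absent direct path** (four measures)
- *b* = 0, *a* = 0.5 (n = 50): 5%.
- *a* = 0.3, *b* = 0.1 to 0.2 (n = 40-50): about 5-8%.

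**School random intercept** (5 schools of 10, correlation with time one 0.3, 300 runs per setting, many convergence warnings, so approximate)
- *u* varying between teachers: 20% (*a* = 0.5, *b* = 0.3) and 60% (both 0.5).
- *u* half at school level: 13% and 35%.

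**School-level confounding alone.** With the school effect set at 20-30% of engagement variance and 10-20% of residual practice variance, correlated 0.8-1.0, the total rate is 7.4-11.8% under a random intercept and 4.6-5.4% with school indicators. The excess is therefore about 2 points (7.4 − 5.4) to 7 points (11.8 − 4.6).

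**Imperfect measurement.** With both paths at 0.5 and an assumed reliability of 0.7 for *u*, the adjusted model still rejects in 9-11%.

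**The case against.** **The stated target is an association.** The hypothesis and the analysis section speak of association and prediction. In the simulations the association given time-one practice is real, so a significant result correctly answers that literal question. This stands: the result is false only if it is read as fidelity improving practice. The conceptual framework invites that reading, but the analysis section does not make it.

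**A stronger reading is tempting.** A reader might infer that if context predicts both engagement and practice, as hypothesised, the fidelity hypothesis will tend to be confirmed even when fidelity does nothing. The article does not support that. Its wording fits equally well a chain in which context acts on practice only through engagement, and then there is no inflation. The conceptual framework allows a direct effect but says only that it may exist. The hypothesis also names engagement alone among the fidelity domains; exposure appears only as an outcome to be examined.

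**The largest rates are extreme.** Paths of 0.5 mean one characteristic explains 25% of time-two variance on top of 25% from time-one practice. Together that is the 50% ceiling the article allows for baseline outcome and all covariates. The 44-52% figures should not be taken as expected.

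**Other covariates may be intended.** The power section mentions further baseline covariates, and a condensed article may leave covariate lists to the analysis plan. But that mention belongs to the power calculation for the post-intervention outcomes of aim two. For aim three the article names outcome, predictors and control, and sends the contextual factors to other models.

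**School indicators have a cost.** Adherence describes delivery in large-group training and school-group coaching, so it may hardly vary within a school. With school indicators in the four-domain model its coefficient might not be estimable. This stands and limits the remedy.

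**Conclusion.** The point holds in a limited form. The fidelity model omits, as far as the article states, baseline characteristics that the article expects to bear on both engagement and practice. If such a characteristic has a direct effect on practice, the estimated fidelity-practice association will partly reflect it.

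For moderate assumed paths the inflation is modest to material: about 9-11% at 0.3 and 21-25% at 0.4, against 5% nominal. It vanishes without a direct path. These rates rest on assumed path values, a single confounder and a true fidelity effect of zero; the article supplies none of these. School-level confounding adds little, and only under strong assumed correlation.

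The consequence is limited to interpretation of aim three, which the power section calls exploratory (its parenthesis names contextual moderators). The randomised aim-two comparison is not affected. This is a minor improvement.

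**What to change.** In Analyses for aim three:

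1. Add baseline teacher self-efficacy, which the hypothesis names, to the four-domain fidelity model. Motivation for change, also collected, may be added if wanted. Fix the choice before the data are finalised; the Trial status section says they have not been.
2. Report the model with time-one practice only beside the adjusted one, and describe both as associations.
3. As a separate sensitivity analysis for exposure and engagement only, enter the five schools as indicators so that the comparison is within school. Keep these indicators out of the four-domain model.

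**Cost.** No new data are needed. The stated model has six fixed coefficients (intercept, four fidelity measures, time-one practice); the main change adds one or two, for 40-50 teachers. The school indicators take about four more in the sensitivity model. Several school-level covariates could not be supported with five schools. Some confounding will remain if the covariates are measured with error or if other common causes exist, so the adjusted model is less biased under the assumed mechanism but does not show a causal effect.

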## Discussion

Children in Uganda and other SSA countries are burdened by significant unmet mental health needs. Knowledge and resource barriers and shortage of mental health professionals limit the capacity of SSA countries to implement preventive strategies or provide basic mental health services. Task-shifting of mental healthcare duties from professionals to teachers is a potentially cost-efficient strategy for mitigating system-level barriers to optimal child mental health in SSA. Although numerous EBPs have been found to meaningfully improve the lives of children living in disadvantaged environments in developing countries, these EBPs have not been transported to SSA, and the implementation supports and adaptations for successful implementation are not well understood. Also, contextual factors that may impact task-shifting or quality of EBP implementation are rarely studied. In order for task-shifting strategies to be effective and translation of EBPs to low-resource countries to be successful, evidence about the quality and process of program implementation and factors predicting task-shifting and implementation outcomes are paramount. This study addresses these implementation and translational research gaps by examining EBP transportability (to developing countries) and effectiveness, and systematically studying factors that may contribute to effective task-shifting. Our implementation study has the potential to illuminate the processes and complexities associated with a task-shifting approach to preventive intervention. Furthermore, this study applies implementation and population health frameworks to guide preventive intervention to address mental health needs in Uganda. If the approach and findings from the proposed study are successful, this study will represent the first step in a series of efforts to transport evidence-based interventions to SSA. Knowledge gained from this study can also be applied to guide other EBP dissemination and implementation efforts that utilize task-shifting strategies in SSA countries.

## Trial status

The study began in July 2013. The first six months was a preparation period for obtaining IRB approval, intervention adaptation, training Ugandan mental health professionals and recruitment of schools and teachers. Data collection in 10 schools and implementation in five schools began in January 2014. Data collection is underway. Participant recruitment is expected to end in December 2014. Data have not yet been cleaned or finalized for evaluation.

## Abbreviations

CFIR: Consolidated Framework for Implementation Research
EBP: Evidence-based program
ICC: Intraclass correlation coefficient
RCT: Randomized controlled trial
RE-AIM: Reach/Efficacy-Adoption/ Implementation/Maintenance
SSA: Sub-Saharan Africa
TTIM: Teacher Training Implementation Model
VIF: Variance inflation factor.
